### Recruitment

3.5

This study will be performed at the tertiary care hospital. It will be conducted in accordance with the principles of Good Clinical Practice (GCP). The study protocol was approved by the Institutional Review Board (IRB). Study participants will be recruited through the department of Neurology after the written informed consent. Informed consent can be very challenging in AS patients. Patients may suffer from language deficit and/or other cognitive impairment that can hamper the informed consent procedure. The primary stroke team and/or the physician provider will assess the mental competence of the potential study participant to determine whether they are capable of giving informed consent. Hence, if the patient is ineligible the study will include the legal authorized representative (LAR) as part of the informed consent process. A study team member will obtain both verbal and written consent and will explain the study protocol to the potential participants. All the patients with the diagnosis of AS will be approached for the consent procedure. In addition, a flyer detailing an overview of the study protocol, as well as a copy of the formal consent form, will be given to potential trial participants. After obtaining the informed consent, the study team member will assign a unique study identification number (SIN) and enter the information in the REDCap database. After informed consent, a pre-randomization assessment for every recruiting patient will be done, evaluating their medical records for any autoimmune and/or inflammatory disorders.

### Data analysis and sample size

3.6

The study team along with the core statistical division will evaluate all the study trial outcomes. One Way Analysis of Covariance (ANCOVA) will be employed, followed by post hoc tests while adjusting for multiple comparisons using the Sidak adjustment. As a secondary analysis, we will also look at the correlation network of these cytokines after stratification by sex and race/ethnicity. According to the ANCOVA model, based on 80% power and 5% significance level, the minimum sample size is 420 AS participants. The primary exposures are biological sex (male, female) and race/ethicity (American Indian/Alaskan Native, Asian/Pacific Islander, African American, Whites, and Hispanics). Confounding variables adjusted in the model include age, vascular risk factors, infarct size, and identified stroke etiologies. Matched controls will be used for the comparison and evaluation of the difference among age, gender, and race/ethnicities.

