## Trial objective

2

The primary objective of the *“*Cytokine Registry In Stroke Patients (CRISP)” is to evaluate

1.the plasma concentration and time course of these pro- and anti-inflammatory cytokines and interleukins2.identification and establishment of a blood base bio-marker that can corroborate with the neurological outcome in these AS patients.

Our primary hypothesis is that temporal change in any one or more cytokine or interleukin levels during this early critical phase could be an important predictor of stroke severity. Moreover, separate sub-studies will explore and compare plasma cytokine levels based on gender, race, and ethnicity.

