### Study design

3.1

This is a prospective patient cohort registry (NCT03297827). Six hundred patients with the diagnosis of AS (IS and HS) will be recruited over the period of 3 years (2018–2021). The overview of the study design is presented in Figure 1. Plasma samples will be collected on admission and after 24 h. Plasma ILs (1, 4, 6, 10, 17, 23, 33, 36, and 37), platelet-derived growth factor (PDGF), vascular endothelial growth factor (VEGFM), tumor necrosis factor (TNF-a), ANNULIN, matrix metallopeptidase (MMP) 9 and 12, nuclear factor kappa-light-chain-enhancer of activated B cells **(**NFk-B), myeloperoxidase (MPO), glia-maturation factor (GMF), SI00 calcium-binding protein B (S100B), and GM6001 will be measured using enzyme-linked immunosorbent assay (ELISA).

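### The stated Sidak step covers only post hoc group contrasts; it controls error neither across the 20 analytes nor for the stroke-severity hypothesis

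*Protocol article*

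**What the plan says.** All references are to the protocol article.

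- **Hypothesis.** Section 2 (Trial objective) states a union hypothesis: "temporal change in any one or more cytokine or interleukin levels" early after stroke could be an important predictor of severity. One positive molecule is enough. The sex and race/ethnicity comparisons are described there as separate sub-studies.
- **Analytes.** Section 3.1 (Study design) lists "Plasma ILs (1, 4, 6, 10, 17, 23, 33, 36, and 37" (nine), then "platelet-derived growth factor (PDGF" (one), then "vascular endothelial growth factor (VEGFM), tumor necrosis factor (TNF-a), ANNULIN, matrix metallopeptidase (MMP) 9 and 12" (five), then NFk-B, MPO, GMF, S100B and GM6001 (five). None is named as primary. Each is measured at admission and 24 hours later.
- **Analysis.** Section 3.6 (Data analysis and sample size) plans a one-way ANCOVA, "followed by post hoc tests while adjusting for multiple comparisons using the Sidak adjustment". The primary exposures given with it are sex (two levels) and race/ethnicity (five levels).
- **Significance level.** The only one appears in the sample-size sentence: "based on 80% power and 5% significance level, the minimum sample size is 420 AS participants". Section 3.1 plans to enrol 600.

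**The concern.** Post hoc tests after a one-way ANCOVA are, on the natural reading, contrasts between groups for one outcome. For race/ethnicity there are 5 x 4 / 2 = 10 pairwise contrasts, and Sidak controls error over those. Sex has a single contrast, so Sidak changes nothing. In neither case does the step look across analytes.

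The stroke-severity hypothesis is further away still. Its predictor is the change in an analyte and its outcome is severity, so group contrasts by sex or race/ethnicity do not test it. A hypothesis that any one of many molecules can satisfy is where control across molecules matters most, and none is stated.

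The Abstract sets out to validate these molecules as biomarkers, and section 2 aims to establish one. A positive finding from an uncontrolled search could be reported as such a biomarker when the search alone could well have produced it.

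**Working it through.** **Inputs from the article**
- Analytes: 9 + 1 + 5 + 5 = 20 (section 3.1).
- Significance level 0.05, power 0.80, minimum N 420 (section 3.6); planned N 600 (section 3.1).
- Exposures: sex, 1 degree of freedom; race/ethnicity, 4 degrees of freedom.

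**Assumptions, not in the article**
- Each analyte is tested at 5%.
- All null hypotheses are true.
- Correlation between test statistics is unknown, so a range is shown.

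**The plan's own figure.** The 420 cannot be reproduced because the article gives no effect size. Under a noncentral-F calculation, 80% power at 5% with N = 420 corresponds to Cohen's f of about 0.137 (sex), 0.170 (race/ethnicity) or 0.195 (ten sex-by-race cells, 9 degrees of freedom). These values are back-solved and serve only to translate the 420 to a stricter level below.

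**Chance of at least one false positive, independent tests:** 1 - 0.95^k.
- k = 20: 1 - 0.95^20 = 0.642
- k = 10 (nine interleukins and TNF-a): 1 - 0.95^10 = 0.401
- k = 13 (adding PDGF, VEGF and GMF): 1 - 0.95^13 = 0.487
- The value first passes 0.50 at k = 14.

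**The same for 20 equally correlated tests,** by simulation with 100,000 draws. Each statistic is sqrt(rho) times a shared normal plus sqrt(1 - rho) times its own normal. The 1-df test is two-sided; the 4-df test sums four such squares.

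| Pairwise correlation | 1-df test | 4-df test |
|---|---|---|
| 0 | 0.641 | 0.640 |
| 0.3 | 0.540 | 0.549 |
| 0.4 | 0.484 | 0.499 |
| 0.5 | 0.415 | 0.439 |
| 0.8 | 0.223 | 0.240 |
| 0.9 | 0.156 | 0.167 |

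Even at 0.9 the rate is about three times 5%.

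**Adjusted level for 20 analytes.** Bonferroni, which is also Holm's first step: 0.05/20 = 0.0025. Sidak: 1 - 0.95^(1/20) = 0.00256.

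**Power at 0.00256,** holding f at the value that gives 80% at 5% with N = 420:

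| Test | Power, N = 420 | Power, N = 600 | N for 80% |
|---|---|---|---|
| Sex, 1 df | 0.412 | 0.628 | 798 |
| Race/ethnicity, 4 df | 0.421 | 0.673 | 724 |
| Ten cells, 9 df | 0.419 | 0.695 | 693 |

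These are close to the least favourable case. Holm relaxes the level after each rejection, and Benjamini-Hochberg does so as more analytes show small p-values.

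**The case against.** The strongest reply is that this is a condensed article, that an analysis plan not shown may define the families, and that defining them is ordinary analysis-plan content. That would answer a complaint of silence. But the article is not silent. It names a multiplicity method, places it on post hoc tests, and gives a sample size at 5% with no allowance for many analytes. A later plan that added control across analytes would change what the 420 delivers.

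Several stronger readings are tempting, and the article does not support them.

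- *A false positive is more likely than not.* For one family of 20 this holds only below a correlation of roughly 0.4. It fails even under independence if the family is 10 or 13 molecules. The article gives no correlations, though it plans a correlation network of the cytokines. Counting both exposures (40 tests, the two exposures taken as independent of each other) raises the figure to 87% with uncorrelated analytes, and it stays above 50% up to a correlation of about 0.7. That, however, pools two questions. All these figures also assume that no analyte has a real effect, while the Introduction cites earlier associations.
- *The plan tests each analyte at 5%.* This is inferred. The 5% stands only in the sample-size sentence, which does not say whether it applies per test or per family.
- *All 20 analytes belong to the primary hypothesis.* Section 2 speaks of cytokines and interleukins, and section 3.4 distinguishes cytokines from other analytes. The word is used loosely, so 20 is a possible reading but not a fixed one.
- *There are 80 tests (20 analytes, two exposures, two times).* The article never sets this out. Temporal change is one quantity per analyte, so the two samples do not double the count for severity.

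These points limit the size of the claim. None supplies control across analytes.

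**Conclusion.** The concern holds in a limited form. As written, the plan's only multiplicity control acts on group contrasts after an ANCOVA. It leaves error across analytes uncontrolled and does not bear on the stroke-severity hypothesis. An exploratory label would not excuse this, given the stated aim of validating and establishing a biomarker.

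The size depends on how many molecules count and how correlated their tests are. With 5% per analyte and all nulls true, the plausible range runs from about 64% (20 independent tests) through 42 to 44% (20 at correlation 0.5), with about 40% for 10 independent tests. No case examined comes near 5%. The secure conclusion is that the error rate is several times nominal; whether it exceeds one half cannot be settled from the article.

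**What to change.** Treat the two questions as separate families and say so in section 3.6 or the analysis plan.

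1. **Stroke severity.** State which molecules form the family. Then either name one primary analyte, tested at 5%, or control family-wise error across the family. Holm is simple and valid under any dependence but does not exploit correlation; permutation max-T does, and so recovers some power.
2. **Sex and race/ethnicity.** For each exposure, apply Benjamini-Hochberg control of the false discovery rate across the analyte omnibus p-values. Run Sidak contrasts only for analytes that pass.
3. **Sample size.** Say whether the 5% is per test or per family, and restate the power or the detectable effect at the adjusted level.

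The writing cost is about one paragraph, with no new data. The statistical cost is lower power per analyte: roughly 41 to 42% at 420 and 63 to 70% at 600 under the strict 0.05/20 level, if 420 gives 80% at 5%. Reaching 80% there would take about 693 to 798 patients. Restating the power or detectable effect is enough; larger enrolment is not being asked for. Naming a single primary analyte avoids the power loss for the severity question, but confines the confirmatory claim to that molecule.

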## Introduction

1

Stroke is a neurologic deficit occurring due to interruption of cerebral blood flow or from bleeding by a ruptured blood vessel in the brain.^[1,2]^ According to World Health Organization (WHO), it is the second leading cause of deaths worldwide.^[3]^ In the United States (US), it is the fifth leading cause of mortality killing around 140,000 Americans each year and the leading cause of morbidity and complex disability.^[4,5]^

During acute stroke (AS), the deprivation of oxygen, glucose, and other nutrients to the brain causes dysfunction of the neurovascular unit. Additionally, the breakdown of the blood–brain barrier, and induction of the inflammatory cascade results in subsequent brain damage.^[6,7]^ This is characterized by an increase in multiple pro-inflammatory and decrease in anti-inflammatory cytokines, which also correlates with progression of stroke injury.^[6,8]^ Various pro-inflammatory cytokines are observed in experimental models and in stroke patients that may correlate with infarct size and stroke outcomes.^[9–14]^ Cytokines and interleukins including TNF-α, interleukin (IL)-1, IL-6, and IL-10, have been studied as therapeutic and prognostic markers in AS.^[10,12,15,16]^ IL-10 is an anti-inflammatory molecule, observed to be associated with negative feedback, whereas IL-6 and TNF-α are reported to be increase in both ischemic and hemorrhagic stroke patients.^[11,16,17]^ Moreover, glial cell markers such as S100B and various other cytokines have also been reported to be associated with infarct size, neurological outcome, and prognosis among these patients.^[10,17–21]^

The inflammatory mechanism and the interaction between the pro- and anti-inflammatory cytokines in AS patients is still ambiguous. Although, studies have indicated changes in systemic cytokine profile in response to experimental stroke, few studies have assessed peripheral cytokine levels in human stroke patients and their association with the neurological outcome.^[10]^ As such, for the use of cytokines as potential biomarkers and prognosis of stroke, it is important to design clinical stroke studies on peripheral cytokine expression that focuses on the temporal profile, comorbidities, and demography.

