### Study outcomes

3.4

The primary objective of this study is to measure the levels of the reported cytokines and other analytes that have a continuous measure, from the plasma of AS patients using standardized ELISA kits. The primary exposures are biological sex (male, female) and race/ethnicity (American Indian/Alaskan Native, Asian/Pacific Islander, African American, Whites, and Hispanics). Confounding variables to adjust for are age, vascular risk factors, medications (anti-inflammatory), infarct size, stroke onset to presentation time, and identified stroke etiologies (based on TOAST criteria).

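### Infarct size arises after sex and race/ethnicity are fixed but is adjusted for as a confounder, so the ANCOVA need not estimate the total group difference in cytokine level

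*Protocol article*

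**What the plan says.** Section 3.6 (Data analysis and sample size) names the exposures: "The primary exposures are biological sex (male, female) and race/ethicity (American Indian/Alaskan Native, Asian/Pacific Islander, African American, Whites, and Hispanics". Section 3.4 (Study outcomes) gives the measured quantity; the aim is to "measure the levels of the reported cytokines and other analytes that have a continuous measure, from the plasma of AS patients". Section 3.6 then lists the ANCOVA covariates: "Confounding variables adjusted in the model include age, vascular risk factors, infarct size, and identified stroke etiologies". Section 3.4 also gives infarct size this role: "Confounding variables to adjust for are age, vascular risk factors, medications (anti-inflammatory), infarct size, stroke onset to presentation time". The abstract lists it among the confounding variables too. The ANCOVA is the only adjusted model described; the secondary analysis is a correlation network.

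On how inflammation and injury relate, the Introduction says that "induction of the inflammatory cascade results in subsequent brain damage" and describes a cytokine shift "which also correlates with progression of stroke injury". On infarct size by name it is weaker: "Various pro-inflammatory cytokines are observed in experimental models and in stroke patients that may correlate with infarct size and stroke outcomes". It also describes injury that arises directly: "the deprivation of oxygen, glucose, and other nutrients to the brain causes dysfunction of the neurovascular unit". Section 2 (Trial objective) hypothesises that early cytokine change predicts stroke severity, and says that sub-studies will compare plasma cytokine levels by gender, race and ethnicity.

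**The concern.** A covariate that arises after the exposure can be a mediator, a consequence of the outcome, or a predictor unrelated to group. Only in the last case does adjustment leave the total group difference unchanged. The article's account of the disease makes the first two roles plausible for infarct size. Inflammation is said to produce later damage, and severity is what the cytokines are meant to predict. Yet infarct size is held constant when the cytokines themselves are compared between groups.

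At stake is what the sex and race/ethnicity contrasts mean. The abstract and section 2 promise a comparison of cytokine levels between groups. A model with infarct size in it answers a different question, the difference among patients with equal infarct size. If infarct size is a consequence of the cytokine, even that contrast has no simple causal reading. No section says that an infarct-independent difference is the target.

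**Working it through.** **The plan's own figure.** Section 3.6 gives a minimum of 420 participants at 80% power and 5% significance, without an effect size, so it can be neither reproduced nor refuted. With a noncentral F calculation and five covariates (assumed), 420 corresponds to f = 0.137 for a 1-df comparison and f = 0.170 for a 4-df comparison. The point does not depend on it; it serves below only to set a scale for power.

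**Inputs.** From the article: exposures S (sex, two levels; race/ethnicity, five), continuous outcome C (plasma level), covariate I (infarct size). Assumed, because the article does not give them: within-group correlation r between C and I of 0.3, 0.5 or 0.7; direct group difference β = 0.30; residual variances of 1. Write b = r/√(1 − r²), which is 0.314 for r = 0.3 and 0.577 for r = 0.5.

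**Step 1: I purely a consequence of C.** C = βS + e, I = bC + u. The within-group slope of C on I is b/(1 + b²), and the groups differ in I by bβ. The adjusted coefficient is β − bβ × b/(1 + b²) = β/(1 + b²) = β(1 − r²).
- r = 0.3: 0.30 × 0.91 = 0.273, a loss of 9%
- r = 0.5: 0.30 × 0.75 = 0.225, a loss of 25%
- r = 0.7: 0.30 × 0.51 = 0.153, a loss of 51%

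**Step 2: I a mediator.** I = gS + v, C = βS + bI + e. The total difference is β + bg; the adjusted one is β.
- g = +0.30: totals of 0.30 + 0.094 = 0.394 (r = 0.3) and 0.30 + 0.173 = 0.473 (r = 0.5); both are estimated as 0.30.
- g = −0.30: totals of 0.206 and 0.127; both are again estimated as 0.30, so adjustment enlarges the difference.

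**Step 3: I affects C but does not differ by group.** This is step 2 with g = 0. Total and adjusted differences are both 0.30, with no bias.

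**Step 4: I a consequence of C that also differs by group through another path.** I = gS + bC + u. The adjusted coefficient is β(1 − r²) − g·r√(1 − r²).
- g = +0.30: 0.273 − 0.086 = 0.187 (r = 0.3); 0.225 − 0.130 = 0.095 (r = 0.5)
- g = −0.30: 0.273 + 0.086 = 0.359; 0.225 + 0.130 = 0.355

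Regressions on 2,000,000 simulated subjects agree for r = 0.3 / 0.5:
- step 1: 0.272 / 0.225
- step 2 (g = +0.30): totals 0.397 / 0.471, adjusted 0.302 / 0.298
- step 3: adjusted 0.299 / 0.299
- step 4: 0.187 / 0.096 (g = +0.30) and 0.357 / 0.354 (g = −0.30)

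**Step 5: power, under step 1 only.** The residual SD also falls, to √(1 − r²), so the standardised difference is multiplied by √(1 − r²): 0.954, 0.866 and 0.714. Take an illustrative two-group contrast with equal groups and 80% power at 420 (standardised difference about 0.27). Power becomes 76%, 68% and 52% for r = 0.3, 0.5 and 0.7. At the planned 600 it falls from 92% to 89%, 83% and 67%.

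**The case against.** A reader might infer that the article's own disease model makes infarct size a product of the measured inflammation, so that adjustment must shrink the group differences. The text does not support that. It says the cascade leads to brain damage, but of infarct size by name it says only that cytokines may correlate with it. It also describes systemic cytokine changes that follow experimental stroke, and injury that comes directly from deprivation. Either direction is open, and steps 2 to 4 show that the bias need not be toward zero. This part of the objection stands in full.

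Measurement time matters too. Section 3.3 lists admission-type imaging; an infarct size read before the 24 h sample cannot be a consequence of the 24 h level. A condensed article may leave that timing to the full protocol, so its absence is no fault here. It does leave the direction unsettled. It does not turn infarct size into a confounder: measured early, it could still be a mediator.

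It can also be said that vascular risk factors and etiology arise after sex and race/ethnicity as well, so the label alone proves little. That is fair. The case against infarct size rests on the further fact that the article's account allows it to be a result of the outcome.

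Finally, patients reach one tertiary hospital within 24 h of onset, and groups may differ in severity through selection. Comparing them at equal infarct size is a legitimate question. It supports an infarct-adjusted model as a second estimand, but not as the only one, since the article nowhere says that this is the difference it seeks.

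**Conclusion.** The point holds in a limited form. The only stated ANCOVA conditions on a variable that arises after both primary exposures and that, on the article's own account, may lie downstream of the outcome. Its estimate need not be the total sex or race/ethnicity difference that the abstract and section 2 set out to compare.

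The size is unknown, because it depends on a correlation and a causal structure that the article does not give. The 9%, 25% and 51% losses hold only if infarct size is purely a consequence of the cytokine. In that case the effect on power is modest at low r and material at r of 0.5 or more. The conclusion that matters is that the sign and size of the departure cannot be known from a single model that contains infarct size.

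**What to change.** In sections 3.4 and 3.6, and in the abstract, take infarct size out of the confounder list for the primary sex and race/ethnicity ANCOVA. Report a second model with infarct size added, in ischemic patients, labelled as the group difference at a given infarct size.

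The cost is wording and one extra model, with no new data. The primary model will have somewhat larger residual variance: its residual SD is 1/√(1 − r²) times that of the adjusted model, which is 1.05, 1.15 and 1.40 for assumed r = 0.3, 0.5 and 0.7. Where infarct size is a consequence of the cytokine, the smaller SD of the adjusted model comes with a biased estimate, so little of real value is given up.

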## Abstract

Inflammation is an important pathophysiological process after an acute stroke (AS). Pro- and anti-inflammatory molecules (cytokines and interleukins) are the key players during this mechanism. Emerging evidence indicate that these molecules can serve as biomarkers of stroke progression and outcome and as novel therapeutics agents. The aim of this study is to explore the temporal changes in these molecules and validate them as biomarker of AS progression and neurological outcome.

The “Cytokine Registry In Stroke Patients (CRISP)” is a prospective cohort study of 600 AS patients presenting to the tertiary hospital with-in 24 h of the onset of symptoms. Plasma cytokines and interleukins will be collected at admission and 24 h after and will be measured using enzyme-linked immunosorbent assay (ELISA) to evaluate the difference in their variation among different gender, race and ethnicity and their association with various neurological outcomes. The primary exposures are biological sex (male, female) and race/ethnicity. Confounding variables include age, vascular risk factors, infarct size, stroke onset to presentation time, and identified stroke etiologies. Matched controls will be used for the comparison and evaluation of the difference among gender and race/ethnicities.

CRISP is a prospective observational study that investigates the role and relationship of molecular biomarkers identifying specific and relevant targets pertinent for monitoring the progression and outcome in AS patients.

Trial Registration: The study is registered on ClinicalTrial.gov: https://clinicaltrials.gov/ (NCT03297827).

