### Data Collection

3.3

Patients who will meet all inclusion criteria/exclusion criteria will be consented. Two sets of plasma samples will be obtained from individual participants; one upon admission to the hospital, and the second sample 24 h apart from the first one. Both sets of blood samples (3–5 mL) will be collected from peripheral veins according to the routine puncture method as standard of care. After centrifugation, the resulting plasma supernatants will be stored at −80°C. The samples will be transported and handled according to the federal guidelines. Additional hospital data will be collected by chart review. This includes last known well or the time of onset of symptoms (according to patient or bystander), the presence of any neurological deficit or hemiparesis (if applicable), demographics, vital functions, neurological examination (NIHSS), imaging include non-contrast CT scan, CT angiography (CTA), digital subtraction angiography (DSA), and/or CT perfusion, clinical data including medical history, comorbidities, medication use, laboratory results, and physical examination will be collected using the chart review. Information regarding the corresponding treatment including door to needle time and door to groin time will be also collected. Other parameters like length of hospital stay, discharge location, and modifies Rankin Scale (mRS) at 3 months will be collected as part of the protocol. All paper consents will be secured in the locked cabinet in the principal investigator (PI) office. The PI's research team will be responsible for consenting, collecting samples, storage in secure refrigerator, running the assays and entering the inferences and other clinical details into a secure REDCap database.^[22]^ REDCap (Research Electronic Data Capture) is a secure, web-based application designed to support data capture for research studies, providing

1.an intuitive interface for validated data entry;2.audit trails for tracking data manipulation and export procedures;3.automated export procedures for seamless data downloads to common statistical packages; and4.procedures for importing data from external sources.

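### The ANCOVA model in Section 3.6 omits onset-to-presentation time and anti-inflammatory medication, which Section 3.4 says to adjust for, so either may be mistaken for a sex or race/ethnicity effect

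*Protocol article*

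**What the plan says.** The article lists the adjustment variables three times.

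- Abstract: "Confounding variables include age, vascular risk factors, infarct size, stroke onset to presentation time, and identified stroke etiologies".
- Section 3.4 (Study outcomes): "Confounding variables to adjust for are age, vascular risk factors, medications (anti-inflammatory), infarct size, stroke onset to presentation time, and identified stroke etiologies".
- Section 3.6 (Data analysis and sample size): "Confounding variables adjusted in the model include age, vascular risk factors, infarct size, and identified stroke etiologies".

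Section 3.6 is also where the model is named: "One Way Analysis of Covariance (ANCOVA) will be employed, followed by post hoc tests while adjusting for multiple comparisons using the Sidak adjustment". The exposures are sex, with two levels, and race/ethnicity, with five.

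Section 3.2 admits patients who present within 24 h of onset. Section 3.3 sets the sampling times: "one upon admission to the hospital, and the second sample 24 h apart from the first one". Neither sample is timed from onset. Section 3.3 also lists last-known-well or onset time, and medication use, among the data to be collected.

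**The concern.** A reader who takes the covariates from Section 3.6, the natural place to look, fits a model without two variables that the plan itself classes as confounders.

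Time is the more important of the two. The primary hypothesis in Section 2 is that cytokine and interleukin levels change during the early phase and that this change predicts severity. On that premise, an analyte level depends on how long after onset the blood was drawn. The clock starts at admission, so two patients with the same disease course can be sampled many hours apart on the biological time scale. None of the four variables in Section 3.6 measures that interval. If one sex or one racial/ethnic group tends to arrive later, part of the time course will appear as a group difference.

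Anti-inflammatory medication works by another route. If its use differs between groups and it alters analyte levels, leaving it out confounds the comparison regardless of sampling time.

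At stake is the interpretation of the declared primary exposures. This kind of bias does not shrink as the sample grows.

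**Working it through.** **Step 1. The three lists side by side.**

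| Variable | Abstract | Section 3.4 | Section 3.6 model |
|---|---|---|---|
| Age | yes | yes | yes |
| Vascular risk factors | yes | yes | yes |
| Infarct size | yes | yes | yes |
| Stroke etiology | yes | yes | yes |
| Onset-to-presentation time | yes | yes | **no** |
| Anti-inflammatory medication | no | yes | **no** |
| Number of items | 5 | 6 | 4 |

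**Step 2. Spread of sampling time.** Presentation is 0 to 24 h after onset (Section 3.2). The first sample is at admission and the second 24 h later (Section 3.3). The first therefore falls at about 0-24 h after onset and the second at about 24-48 h. Each has a range of about 24 h.

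**Step 3. Illustrative size, for a level at one time point.** The documents give no drift per hour, no delay difference between groups and no sex split. Assumptions: drift *b* of 0.02-0.06 SD per hour, delay gap *d* of 1-3 h, no true sex difference, and equal groups of 210 (half of the stated minimum of 420).

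- Bias = *b* × *d*, in SD units.
- Standard error of the difference = √(2/210) = 0.0976 SD.
- Type I error = P(|Z + bias/0.0976| > 1.96).

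| *b* (SD/h) | *d* (h) | Bias (SD) | Bias/SE | Type I error, 210 vs 210 | Type I error, 300 vs 300 |
|---|---|---|---|---|---|
| any | 0 | 0 | 0 | 5.0% | 5.0% |
| 0.02 | 1 | 0.02 | 0.20 | 5.5% | 5.7% |
| 0.04 | 2 | 0.08 | 0.82 | 13.0% | 16.5% |
| 0.06 | 3 | 0.18 | 1.84 | 45.4% | 59.7% |

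The last column uses the planned 600 patients, with SE = √(2/300) = 0.0816. The error grows with the sample because the bias stays fixed while the standard error falls.

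**Step 4. Why these figures do not carry over to the 24 h change.** With linear drift, level = a + *b*·t. A patient first sampled at time t has change = *b*(t + 24) − *b*·t = 24*b*, whatever t is. A delay gap then adds no bias to the change. Bias in the change would need a non-linear time course, for which the documents give no figures.

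**Step 5. Cost of restoring the two variables.** The stated 420 (80% power, 5% level) cannot be reproduced because no effect size is given, so I worked back from it. With a noncentral F, noncentrality N·f² and each covariate counted as one degree of freedom, 420 implies f = 0.137 for sex. Going from four to six covariates moves the error degrees of freedom for sex from 420 − 2 − 4 = 414 to 420 − 2 − 6 = 412. The required number moves from 420 to 421, and power at 420 stays at 80.0%.

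**The case against.** The strongest reply is that Section 3.6 says the adjusted variables *include* four items, which need not be exhaustive. Section 3.4 states plainly that time and medication are to be adjusted for, and the abstract repeats time. Section 3.6 may be an abridged restatement, and an analyst who follows Section 3.4 avoids the problem. This is a fair reading of the intention, but it does not settle the text. Section 3.6 is the only place that describes the model, and following it literally leaves out confounders that the plan names. If the list is open-ended, the covariates are not fixed at all. Nor is this a detail left to an analysis plan, because the article states the covariates and contradicts itself.

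It is also fair to say that the size is unknown. The 45% needs both upper assumptions at once, and 0.06 SD per hour amounts to 0.06 × 24 = 1.44 SD over a day. The bias arises only if delay differs between groups and the analyte varies with time since onset.

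Four stronger readings are tempting and are not supported:

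- **That reperfusion treatment is a third omitted confounder.** Section 3.3 says of it: "Information regarding the corresponding treatment including door to needle time and door to groin time will be also collected". No list names it, so nothing is contradicted. The article does not place the first draw before or after treatment. Treatment also follows the exposures and may lie on the causal path.
- **That the same error rates apply to the 24 h change.** Step 4 shows that linear drift gives none.
- **That everything needed for exact timing is already collected.** Onset or last-known-well time and medication use are listed; blood-draw times are not.
- **That sampling time explains both omissions.** It explains only the first.

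**Conclusion.** The point holds. The abstract, Section 3.4 and Section 3.6 give five, six and four adjustment variables for the same analysis. The model as written leaves out onset-to-presentation time and anti-inflammatory medication. This contradiction rests on the text alone.

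The consequence is conditional. For analytes that change with time since onset, a difference in arrival delay by sex or race/ethnicity can be attributed to the exposure. The range of 5.5% to 45% is an illustration for single-time levels under assumed drift and delay, and without a delay gap the rate is 5%. It should not be quoted as an estimate for this study. The effect of omitting medication is a second possible bias and cannot be quantified from the documents.

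**What to change.** Reconcile the abstract, Section 3.4 and Section 3.6 to one list, and make the Section 3.6 sentence exhaustive. Add to that model onset (last-known-well)-to-presentation time and anti-inflammatory medication. A non-linear term for time is preferable, since a straight line over 24 h may not fit a cytokine response. If blood-draw times are recorded, use onset-to-sample time for each sample instead.

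The cost is a change of wording in Section 3.6, a matching change in the abstract, and a few degrees of freedom out of more than 400. For example, linear and quadratic time plus one medication indicator use three. On the one-degree-each count above, the required number rises by one, from 420 to 421. Section 3.3 already lists onset or last-known-well time and medication use; onset-to-sample time would also need the draw times.
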